### Methods for additional analyses (e.g., subgroup analyses) {20b}

#### Temporality of PE effects

It is expected malaria incidence changes by seasonality (rainy vs dry) and year. To examine the temporality of malaria incidence rates and the PE effect, a supplementary analysis will be performed by adding the seasonality (Jun-Dec/wet/peak and Jan-May/dry/low) and year (1 and 2) and their interaction with intervention to the covariate list in the cloglog models used for analyzing the first-time and overall infections. The PE will be estimated by seasonality and year.

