**Methods:**

This trial is designed as a cluster-randomized, placebo-controlled, double-blinded clinical trial. Sixty clusters will be randomly assigned in a 1:1 ratio to receive spatial repellent or placebo. A total of 6120 children aged ≥6 months to 10 years of age will be randomly selected from the study clusters, enrolled into an active cohort (baseline, cohort 1, and cohort 2), and sampled monthly to determine time to first infection by smear microscopy. Each cohort following the implementation of the intervention will be split into two groups, one to estimate direct effect of the spatial repellent and the other to estimate degree of diversion of mosquitoes and malaria transmission to unprotected persons. Malaria incidence in each cohort will be estimated and compared (primary indicator) to determine benefit of using a spatial repellent in a high, year-round malaria transmission setting. Mosquitoes will be collected monthly using CDC light traps to determine if there are entomological correlates of spatial repellent efficacy that may be useful for the evaluation of new spatial repellents. Quarterly human landing catches will assess behavioral effects of the intervention.

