**Table Tabb:** 

	Study period			
	Baseline	Intervention		Close-out
**Timepoint**	(Mar 2021–Jul 2021)	(Aug 2021–Jul 2022)	(Aug 2022–Jul 2023)	(Aug 2023–Jan 2024)

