#### Primary hypothesis on first-time malaria infection

The sample size determination on the required number of subjects (HHs) per cluster for testing the primary hypothesis is based on the hazard rate comparison in the proportional hazards regression model [36, 37]. With the following specifications: 1-sided type I error rate = 5%, true PE = 30%, a between-cluster CV of hazard rate = 44% (based on historical data collected from Kenya), one interim analysis for efficacy and non-binding futility with the O’Brien-Fleming error spending function when 50% of events have been collected then 1055 first-time malaria events will need to be observed to reach 85% power in testing the primary hypothesis on PE.

With a baseline first-time malaria infection hazard rate of 3.0 per person-year, 30 clusters per treatment arm, with 20 subjects (HHs) per cluster are expected to yield 1055 independent first-time malaria events within a 12-month follow-up period per cohort post randomization to yield 85% power. If, by the end of the 2-year study, 1055 independent malaria events are not reached, the study may extend until 1055 events are collected without inflating the type I error rate in the testing of the primary hypothesis. Factoring in a LTFU rate at 35%, the required sample size is 28 subjects (HHs) per cluster, which will be split in half between the two sequential cohorts with 14 subjects (HHs) per cohort per cluster.

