#### Cohort follow-up

Children enrolled in the baseline cohort will be followed for a 4-month period, prior to the distribution of the study products. To avoid substantial LTFU due to study fatigue, two independent cohorts (cohort 1 and cohort 2) will be recruited and followed with intervention each for 12 months (see Trial Design {8}); therefore, the total period of follow-up will be 28 months; 4-month baseline phase and 24 months after deployment of the intervention. Cohort 1 will end 12 months after the SR is deployed. Cohort 2 will be recruited, enrolled, and cleared of infection with a treatment dose of AL at enrolment as described above. Children enrolled in the baseline cohort will be eligible for inclusion in cohorts 1 or 2; however, those children enrolled in cohort 1 during intervention will not be eligible for inclusion in cohort 2. The recruitment, enrolment, screening, and follow-up of cohort 2 will be the same as described for the cohort 1.

Follow-up visits for each baseline, cohort 1, and cohort 2 will alternate between a clinic visit (monthly; passive case detection) and a home visit (every 2 weeks; active case detection). Routine blood sampling will occur at the clinic, whereas blood sampling will only occur during home visits if subjects have reported history of fever in the last 48 h. Study participants will be issued with an appointment card where all upcoming appointments will be recorded. In between the clinic appointments, community interviewers may refer participants to the clinic for additional assessment by the clinical officer using the participant referral slip. Participants will be instructed to visit a study health facility for any unscheduled sick visits, or they will be visited at their home if they cannot reach the clinic. Missed visits will be considered minor protocol deviations and will be collated and reported to KEMRI Scientific Ethical Review Unit (SERU) and UND along with the annual progress report. Three consecutive missed visits will prompt consideration for LTFU and withdrawal from the study.

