## Trial status

Under protocol version 7 from November 20, 2020, recruitment for the baseline cohort began March 1, 2021, and final subject enrolment was completed April 2, 2021.

The study has currently completed the baseline phase (as of July 31, 2021), whereby participants have been recruited, screened, and enrolled and followed up without intervention for 4 months. Baseline data analyses are ongoing to verify underlying assumptions of malaria incidence, coefficient of variation, and loss to follow-up. Recruitment, screening, and enrolment of subjects for follow-up with intervention is scheduled to commence in August 2021.

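### Protective efficacy by season cannot be read as seasonal for first-time infections, because both cohorts start in August and most children have had their first infection before January

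*Protocol article*

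**What the plan says.** Under Temporality of PE effects, the protocol article plans a supplementary analysis by "adding the seasonality (Jun-Dec/wet/peak and Jan-May/dry/low) and year (1 and 2) and their interaction with intervention to the covariate list". The terms go into both sets of models, that is "in the cloglog models used for analyzing the first-time and overall infections", and PE is then to be estimated by season and by year.

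The Participant timeline places the first intervention cohort in "Aug 2021–Jul 2022" and the second in "Aug 2022–Jul 2023". Cohort follow-up confirms that "two independent cohorts (cohort 1 and cohort 2) will be recruited and followed with intervention each for 12 months", and Trial status adds: "Recruitment, screening, and enrolment of subjects for follow-up with intervention is scheduled to commence in August 2021".

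The models differ between endpoints. For first-time infection, the primary-endpoint section gives a cloglog model with treatment arm, baseline covariates that are not listed, and a cluster random effect. For overall infections, the secondary-endpoint section adds a random effect for the individual child. The section on PE without baseline covariates shows that visit enters these models as a categorical predictor.

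The sample-size section for the primary hypothesis supplies the hazard: "With a baseline first-time malaria infection hazard rate of 3.0 per person-year". It assumes a true PE of 30%, which is a hazard ratio of 0.7.

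**The concern.** A child leaves the first-time risk set at the first infection. When every child enters in about the same month, calendar season is fixed by follow-up month, and a second cohort starting in the same month a year later does not break that link. A difference in first-time PE between the two seasons could then reflect season, waning or some other effect of time since enrolment, and the model has no information to tell these apart.

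The second problem is conditional. If children in the same cluster differ in risk in ways the model does not capture, the higher-risk children have their first infection early, and sooner in the placebo arm. Those still at risk in January are then more strongly selected for low risk under placebo, and the hazard ratio drifts towards 1 even if the repellent works equally well all year.

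At stake is a published pair of seasonal PE figures that a policy reader could take as evidence of weaker protection in the low season.

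**Working it through.** **Inputs from the protocol.** Hazard 3.0 per person-year; hazard ratio 0.7, so 3.0 × 0.7 = 2.1 in the repellent arm; 30 clusters per arm; 20 children per cluster before allowance for loss; between-cluster CV 0.44; 1055 events for 85% power; one-sided 5%.

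**Inputs assumed.** All children start on 1 August; no loss to follow-up; flat hazard unless stated; between-child risk follows a gamma distribution with mean 1 and variance θ.

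**Step 1: reproduce the plan's figures.**
- Var(log HR) = 4/1055 + 2 × 0.44²/30 = 0.00379 + 0.01291 = 0.0167, so SE = 0.129.
- Power for a fixed one-sided 5% test is 86.8%. With the stated interim and final boundaries it is 86.3%, and 84.3% if the futility boundary is obeyed. All are close to 85%.
- Expected first events in 12 months are 600 × (1 − e^−3.0) + 600 × (1 − e^−2.1) = 570 + 527 = 1097. With the 44% cluster variation this falls to 1041 (gamma) or 1047 (lognormal), close to 1055. Reading 3.0 as a constant hazard over 12 months therefore matches the plan.

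**Step 2: who is still at risk, from S(t) = e^(−ht).**

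| Date | Months | Placebo | Repellent |
|---|---|---|---|
| 1 January | 5 | e^−1.25 = 28.7% | e^−0.875 = 41.7% |
| 1 June | 10 | e^−2.5 = 8.2% | e^−1.75 = 17.4% |

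**Step 3: where the first events fall.** The total per pair of children is 0.950 + 0.878 = 1.828.
- August to December: (0.713 + 0.583)/1.828 = 71%.
- January to May: (0.204 + 0.243)/1.828 = 24.5%.
- June to July: (0.032 + 0.051)/1.828 = 4.6%.

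Only about 6% of the first events labelled wet season (4.6/75.5) come from late follow-up. The wet–dry contrast is nearly an early–late contrast.

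**Step 4: depletion bias if θ > 0.** With true PE constant at 30%, the hazard ratio among children still at risk is HR(t) = 0.7(1 + 3.0θt)/(1 + 2.1θt). At θ = 0.5:
- 1 January (t = 5/12): 0.7 × 1.625/1.4375 = 0.791, PE 21%.
- 1 June (t = 10/12): 0.7 × 2.25/1.875 = 0.840, PE 16%.

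Averaged over the risk sets in each season (large-sample limit, no cluster effect or covariates), and compared with 250 simulated trials per θ that fitted the cloglog model with categorical visit and a cluster random effect:

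| θ (assumed) | Limit, Jun–Dec / Jan–May PE | Simulation, Jun–Dec / Jan–May PE |
|---|---|---|
| 0 | 30.0 / 30.0% | 29.7 / 28.7% |
| 0.5 | 25.2 / 18.6% | 24.5 / 20.2% |
| 1.0 | 22.5 / 13.5% | 22.8 / 16.5% |

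The gap is about 7 to 9 points in the limit and 4 to 6 points in the simulation. If the dry-season hazard is half the wet-season hazard (assumed), the limits are 24.5 / 17.9% and 21.6 / 12.8%, so the picture hardly changes. A lower hazard of 2.0 (assumed) gives 26.0 / 21.2% and 23.6 / 16.4%.

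**Step 5: compare with sampling error.** In the simulation the shift in log HR between seasons is 0.056 at θ = 0.5 and 0.078 at θ = 1.0 (Monte Carlo errors 0.010 and 0.011). The standard deviation of that difference in a single trial is 0.15 to 0.17. At θ = 0 the shift is 0.014 (Monte Carlo error 0.009), which is within simulation error.

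**The case against.** The strongest reply has five parts.

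- **Season is not identical to time since enrolment.** This is right. June and July count as wet and fall in months 11 and 12. They rescue little, because they carry only about 6% of wet-season first events.
- **A reader might infer that depletion alone must make the repellent look weaker in January to May.** The documents do not support that. The bias needs variation in risk between children in the same cluster, left over after the cluster random effect and the baseline covariates. The documents point to such variation (prevalence and net coverage differ by age, under Eligibility criteria) but give no variance. Their one heterogeneity figure, the 44% CV, is between clusters and is modelled. Age is an obvious candidate covariate, age subgroups are analysed separately, and the covariate list may properly be left to the analysis plan.
- **The shift is small beside sampling noise.** This stands. At most it is about half the standard deviation of the seasonal difference, so it would seldom produce a significant interaction. It would still move the reported point estimates.
- **The trial's aims do not depend on it.** A reader might take the abstract's "to determine benefit of using a spatial repellent in a high, year-round malaria transmission setting" as a promise of proof in every season. The words describe the setting. No listed objective mentions season, the analysis is supplementary, and neither the hypothesis tests nor the interim rules use it.
- **The better analysis is already planned.** The same sentence covers overall infections. That makes the repair cheap, but nothing in the article warns against reading the first-time version as seasonal. Nor is the overall model free of the problem: January to May is still months 6 to 10 there too.

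**Conclusion.** The point holds in a limited form. For first-time infections, the seasonal PE cannot be separated from time since enrolment. This follows from the August start of both cohorts and needs no assumption about heterogeneity. At the plan's own hazards, 71% of first events fall before January.

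The added depletion bias is conditional. With residual within-cluster variance of 0.5 to 1.0 (assumed), a constant 30% PE would appear about 4 to 9 points lower in January to May than in June to December; the lower part of that range, 4 to 6 points, comes from simulating the cloglog model with its cluster random effect. With no residual variation the bias is zero.

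The figures also assume a common start on 1 August and no loss to follow-up. If enrolment is spread over about a month, as at baseline, the months shift by up to one and the conclusion is the same. The primary hypothesis test is unaffected. It is a flaw in how one supplementary result can be interpreted, worth correcting before unblinding.

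**What to change.** Under Temporality of PE effects:

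1. Base PE by season on the overall-infection model, in which children return to the risk set and which has a random effect for the child.
2. Drop PE by season from the first-time model, or report it only with a statement that it is confounded with time since enrolment.
3. State that the overall-infection contrast avoids most of the depletion but is still partly aligned with follow-up time, since both cohorts start in August.
4. Keep the year contrast in both models, because the two cohorts start in the same month.

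The change is one of wording. It needs no new data or model, and it costs one supplementary first-time output, which is lost or carries a caveat.

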#### Human behavior adjusted PE analysis

The primary and secondary analyses for the first-time infection, the overall infection, and the examination of relationship between the entomological and epidemiological endpoints will also be carried out by adjusting for the human behavior covariates the cloglog models, including “bed net usage” in the last 24 h (Y or N), “travel outside” (Y or N; an individual-level covariate), and the product application rate in each HH (expected to be close to 100%) if the data are balanced between the Y and N categories on “bed net usage” and “travel outside”, and there is practically/clinically meaningful variation in the product application rate across HHs and clusters.

#### Adjusted HBR analysis

The adjusted HBR at a given time point is calculated as the raw HBR × the proportion of people at the risk of being bitten in each HH. Specifically, in each HH where the HBR data are collected in hourly intervals from 6 pm to 6 am, the number of people indoor, the number of people outdoor, the number of people under bed net indoor, and the number of people sleeping outdoor are also collected. The adjusted HBR indoor = raw HBR × number of subjects not under the protection of bed net/ total number of indoor subject, and the adjusted HBR = raw HBR × number of subjects who sleep / total number of subject outdoor. The analysis specified for the estimating the effects SR on the raw HBR will be applied to the adjusted HBR.

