### Outcomes {12}

The primary outcome measure of this cRCT will be the first-time malaria incidence rate as measured by microscopy in children aged ≥ 6 months to 10 years.

Secondary outcome measures include:
Overall new *Plasmodium falciparum* malaria infections, as measured by microscopy;The first-time and overall *P. falciparum* malaria infections in buffer zones, as measured by microscopy;The first-time and overall *P. falciparum* malaria infections by two age groups (≤ 59 months old; 5 years old to 9 years and 11 months old), as measured by microscopy;Anopheline-human contact (indoor and outdoor) using human biting rate (HBR) as an indicator for all anophelines and by anopheline species, as measured by HLC during 12-h intervals on a quarterly basis;Anopheline survival and population age structure using parity rate as an indicator for all anopheline and by anopheline species, as measured by mosquito ovarian dissections from a sub-sample of anophelines collected during HLC procedures;Anopheline infectivity using sporozoite rate as an indicator for all anopheline and by anopheline species, as measured by laboratory detection of sporozoites in mosquito heads and thoraces from a sub-sample of anophelines collected during HLC and/or CDC light trap collections;Entomological inoculation rate (EIR) as an indicator of transmission intensity for all anophelines and by anopheline species, as measured by calculating the number of sporozoite-infected anopheline mosquitoes captured per person from CDC light trap and/or HLC collections;CDC light trap indoor density for all anophelines and by anopheline species, as measured by light trap collections during 12-h intervals on a monthly basis;Insecticide resistance, as measured by WHO filter paper test and CDC bottle assays during baseline and intervention phase.Adverse events (AEs) and serious adverse events (SAEs), as measured by solicited and unsolicited reports during baseline and intervention phase. Mean, minimum, and maximum frequency and percentage of AEs and SAEs across clusters among enrolled subjects will be summarized by treatment arm.

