## Discussion

ITNs and indoor residual spraying have contributed to substantial reductions in malaria burden since 2000 [1]. However, malaria remains a serious public health concern, particularly in sub-Saharan Africa due to gaps in protection from ITNs and IRS. Supplemental tools such as SRs may address these gaps in coverage and contribute to further reductions in malaria burden [5, 7, 45].

SRs, like the Mosquito Shield™, are devices containing volatile chemicals that disperse in air under ambient conditions (no requirement of electricity or heat to volatilize); they can be placed inside or around houses. The volatile chemicals introduced into the air repel mosquitoes from entering the treated space and/or disrupt mosquito biting and feeding habits, possibly impacting their survival and reproductive behavior [5]. SR products are envisioned to complement and enhance existing vector control methods due to the continual release of volatile AI which precludes the requirement of mosquito contact with a treated surface.

The role for SR products in malaria public health vector control are likely to be greatest in settings where early-evening and/or outdoor biting by *Anopheles* mosquitoes avoids the effects of ITNs and IRS. In addition, SR product chemicals operate through a different mode of action and laboratory assays have demonstrated behavioral effects against both insecticide susceptible and resistant anopheline and mosquito vectors responsible for transmitting multiple human pathogens [27]. Thus, SRs may serve as a tool in areas where insecticide resistance limits the effectiveness of ITNs and IRS. SRs may also reduce selection pressure for insecticide resistance and thereby maintaining the tools’ natural life span [7].

There are thousands of registered SR products already on the market and used for protection from nuisance biting. Current registered products include sophisticated, expensive products used in the USA and Europe (liquid vaporizers) as well as inexpensive and simpler products (e.g., mosquito coils) that are widely used throughout Africa and Asia. However, there is presently no public sector use of mosquito coils (or any other SR product format) for disease control due to insufficient evidence for WHO policy recommendation.

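### The outdoor adjusted human biting rate counts only people who sleep as at risk, which contradicts the section's own definition and can hide or dilute an early-evening outdoor effect within that additional analysis

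*Protocol article*

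**What the plan says.** The section Adjusted HBR analysis, under Methods for additional analyses {20b}, opens by defining the adjusted rate: "the raw HBR × the proportion of people at the risk of being bitten in each HH". The data come from human landing catches, "in each HH where the HBR data are collected in hourly intervals from 6 pm to 6 am". The counts recorded alongside are people indoors, people outdoors, "the number of people under bed net indoor, and the number of people sleeping outdoor are also collected".

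Two formulas follow. The first is labelled indoor: "The adjusted HBR indoor = raw HBR × number of subjects not under the protection of bed net/ total number of indoor subject". The second carries no label, but its denominator is people outdoors: "the adjusted HBR = raw HBR × number of subjects who sleep / total number of subject outdoor". The section then applies the raw-HBR model to the adjusted values.

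Elsewhere, Outcomes {12} lists "Anopheline-human contact (indoor and outdoor) using human biting rate (HBR) as an indicator" as a secondary outcome. The Discussion says the product's role is "likely to be greatest in settings where early-evening and/or outdoor biting" escapes nets and spraying.

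**The concern.** The definition asks for the proportion at risk. The indoor formula respects it, because its numerator is everyone without a net, awake or asleep. The outdoor formula does not. Someone sitting, cooking or walking outside enters the denominator but not the numerator, and so counts as protected. The article gives no reason for this. The raw HBR is itself measured on collectors who stay awake all night (Who will take informed consent? {26a}), so being awake cannot be what removes the risk.

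The error falls on the exposure the product is meant to address. Collection starts at 6 pm, when people may be outdoors and awake. In any household-hour with no outdoor sleeper, the formula returns 0 whatever the catch. Those zeros reflect sleeping habits rather than absence of mosquitoes, and they would enter the Poisson or negative binomial models, possibly zero-inflated, that are planned for HBR.

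**Working it through.** The article states no adjusted HBR value, so there is no figure to reproduce. The check is algebraic, followed by an example with assumed inputs.

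**1. The two weights side by side.** For one household-hour, let I = people indoors, N = indoors under a net, O = people outdoors, S = asleep outdoors.

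- Indoor weight as written: (I − N) / I, the unprotected share.
- Outdoor weight as written: S / O. The O − S people awake outdoors get weight zero.

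If the outdoor weight is the same in both arms and above zero, it cancels from that hour's ratio of spatial repellent (SR) to placebo, and the hour merely counts for less. If S = 0, the hour contributes 0 in both arms. If O = 0, the weight is undefined.

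**2. One hour (assumed).** Household of 5, O = 4, S = 0, raw outdoor HBR 2 per hour.

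- As written: 2 × 0/4 = 0.
- Everyone outdoors counted, outdoor denominator: 2 × 4/4 = 2.
- Everyone outdoors counted, household denominator: 2 × 4/5 = 1.6.

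**3. One night (assumed), 12 hours from 6 pm.**

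- Placebo raw outdoor HBR: 2, 2, 2, 2, 2, 2, 3, 3, 3, 3, 3, 2 (sum 29).
- People outdoors: 5, 5, 4, 3, 1, 1, 1, 1, 1, 1, 1, 2.
- SR effect: 30% reduction in the first four hours only; behaviour the same in both arms.

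Raw ratios: evening (first four hours) 5.6/8 = 0.70; whole night 26.6/29 = 0.917.

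Adjusted as written:

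| Outdoor sleepers | Evening SR / placebo | Whole night SR / placebo |
|---|---|---|
| None all night | 0 / 0, undefined | 0 / 0, undefined |
| One in each of the five hours from midnight | 0 / 0, undefined | 15 / 15 = 1.00 |
| One in every hour | 1.377 / 1.967 = 0.70 | 21.377 / 21.967 = 0.973 |

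In the third row the evening weights are 1/5, 1/5, 1/4 and 1/3. The evening ratio survives, but those hours carry little of the total.

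**4. Testing the repair.** If only the numerator changes to everyone outdoors, the weight is O/O = 1 and the adjusted value equals the raw value (0.70 and 0.917 again). The adjustment then does nothing. With the household total I + O as denominator, taken as 5 here:

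- Evening weights are 1, 1, 0.8, 0.6. Placebo: 2 × 3.4 = 6.8. SR: 0.7 × 6.8 = 4.76. Ratio 0.70.
- Later hours, same in both arms: 2 × 0.2 × 2 + 5 × 0.2 × 3 + 0.4 × 2 = 0.8 + 3.0 + 0.8 = 4.6.
- Whole night: (4.76 + 4.6) / (6.8 + 4.6) = 9.36 / 11.4 = 0.821.

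The weight now gives more influence to hours when more people are outside. It is also defined (as 0) when nobody is outdoors. These are sums over hours, not model fits. They show the direction and nothing about the size in this trial.

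**The case against.** A reader might infer that the repellent's outdoor evening effect, or outdoor diversion, could not be seen in this trial. The article does not support that. Raw HBR, indoors and outdoors, is a secondary outcome with its own SR/placebo ratio and no behavioural weighting (Effects of SR on entomological endpoints). The diversion objective is assessed through buffer-zone infections and buffer-zone light traps, not through adjusted HBR. The weight is exactly zero only when no one sleeps outdoors, and the article does not say how often that is. Any percentage of evening exposure lost would simply restate an assumed sleeping share.

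The clause also looks garbled. It has no outdoor label and does not say where the subjects sleep. A drafting slip is at least as plausible as a decision to treat awake people as safe. The analysis rests on quarterly catches in 12 of 60 clusters, and no hypothesis test, stopping rule or sample size depends on it.

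All of this stands and limits the consequence. It does not remove the error. The article fixes a numerator and a denominator, and an analyst who follows them computes something other than the quantity defined in the same section.

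**Conclusion.** Wrong as written, and confined to one additional analysis. The outdoor formula contradicts "the raw HBR × the proportion of people at the risk of being bitten in each HH" and the indoor formula beside it. It can hide an early-evening outdoor effect (0 in both arms in hours with no outdoor sleeper) or dilute it (whole-night 0.973 or 1.00 against 0.917 raw in the assumed example). How far it would do so in practice depends on outdoor sleeping, for which the article has no figures. The conclusion rests on two readings: that the unlabelled second formula is the outdoor one, and that its sleepers are those sleeping outdoors. The denominator and the list of counts support both. The raw outdoor HBR, the buffer-zone diversion analyses and the primary endpoint are unaffected.

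**What to change.** In Adjusted HBR analysis, label the second formula as outdoor and restate both parts:

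- **Numerator:** all people outdoors in that hour, awake or asleep. Outdoor net use is not among the listed counts, so everyone outdoors has to be taken as unprotected, and the text should say so.
- **Denominator:** restate it together with the numerator. One option that fits the household-based definition is the household total (indoors plus outdoors) for both weights: indoor (I − N)/(I + O), outdoor O/(I + O).
- **Number sleeping outdoors:** keep it as a descriptive variable.

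The cost is one line of wording. The indoor and outdoor counts are already collected, so no new data are needed. The change should be made before the unblinded analysis.

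### The outdoor formula in the supplementary adjusted HBR analysis gives awake people outdoors zero weight, which contradicts the section's own definition of adjusted HBR and its indoor rule

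*Protocol article*

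**What the plan says.** The section Adjusted HBR analysis, under Methods for additional analyses {20b}, starts with a general definition: adjusted HBR is "raw HBR × the proportion of people at the risk of being bitten in each HH". It says that "HBR data are collected in hourly intervals from 6 pm to 6 am", so the evening hours are covered. Besides the totals indoors and outdoors, it says that "the number of people under bed net indoor, and the number of people sleeping outdoor are also collected".

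Two formulas follow. Indoors, raw HBR is multiplied by "number of subjects not under the protection of bed net/ total number of indoor subject". The second formula has no location label, but its denominator shows that it is the outdoor one: raw HBR is multiplied by "number of subjects who sleep / total number of subject outdoor". The treatment model planned for raw HBR is then to be re-run on the adjusted values.

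On the setting in which the product should matter, the Discussion says that its role is "likely to be greatest in settings where early-evening and/or outdoor biting" escapes nets and indoor spraying. The Background lists early-evening biting and peri-domestic space among the situations in which spatial repellents protect.

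**The concern.** The definition asks for the share of people who can be bitten. A person who is awake outdoors and not under a net can be bitten, yet the outdoor formula gives that person no weight. The same person sitting awake indoors without a net has full weight under the indoor formula. The two rules cannot both express one definition of being at risk.

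At stake is the adjusted outdoor comparison between the arms. As written, it rests only on hours in which someone sleeps outdoors. Outdoor biting on people who are still up, which is the usual form of early-evening outdoor exposure, drops out. A reader would take the result as a behaviour-adjusted outdoor effect when it is an effect on outdoor sleepers.

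**Working it through.** The article gives no numerical result for adjusted HBR, so there is no figure to reproduce. The check evaluates the stated formulas.

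**1. Formulas as written, for one household-hour**

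- Indoor adjusted HBR = indoor raw HBR × (indoors, not under a net) / (all indoors)
- Outdoor adjusted HBR = outdoor raw HBR × (asleep) / (all outdoors)

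**2. Weight given outdoors**

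Take 5 people outdoors (assumed), of whom k sleep. The weight is k/5:

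| Asleep outdoors (k) | Weight |
|---|---|
| 0 | 0/5 = 0 |
| 1 | 1/5 = 0.2 |
| 5 | 5/5 = 1.0 |

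With k = 0 the adjusted value is 0 for any raw catch. With k = 1, the four awake people add nothing and pull the weight down to 0.2.

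**3. One evening hour (assumed counts)**

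Six members are present: 4 outdoors and awake, 2 indoors without nets. Raw HBR is 3 outdoors and 2 indoors.

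- Outdoors as written: 3 × 0/4 = 0
- Indoors as written: 2 × 2/2 = 2.0

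All six are unprotected, but only the two indoors count.

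**4. One night (assumed profile, 12 hourly intervals)**

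- Raw outdoor HBR by hour: 2, 3, 3, 2, 2, 1, 1, 1, 1, 1, 1, 1
- People outdoors by hour: 5, 5, 4, 3, 1, 0, 0, 0, 0, 0, 1, 3

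Someone is outdoors in 7 hours, and raw HBR over those hours is 2 + 3 + 3 + 2 + 2 + 1 + 1 = 14. Nobody is assumed to sleep outdoors in the first four hours, which hold 2 + 3 + 3 + 2 = 10 of the 14. The other three hours hold 2 + 1 + 1 = 4.

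| Share asleep among people outdoors in the later hours | Adjusted outdoor total as written | With everyone outdoors at risk |
|---|---|---|
| 0% | 10 × 0 + 4 × 0 = 0 | 14 |
| 10% | 10 × 0 + 4 × 0.10 = 0.4 | 14 |
| 25% | 10 × 0 + 4 × 0.25 = 1.0 | 14 |

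The first four evening hours contribute 0 in every row.

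**5. Does another reading rescue the formula?**

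The numerator does not say where the subjects sleep. If it meant all sleepers in the household, 4 sleepers with 2 people outdoors would give 4/2 = 2, which is not a proportion. Awake people outdoors would still have no weight. The list of counts collected includes people sleeping outdoors, which fits the first reading.

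**6. What this does to the SR/placebo ratio**

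In each arm the adjusted outdoor total is the sum over hours of raw HBR × sleeping share. Hours with a sleeping share of 0 vanish from both arms. If the product acts differently on evening and late-night biting, the ratio reflects only the hours with outdoor sleepers. If the sleeping share differs between the arms, that difference enters the ratio as well. If the product effect is the same in every hour and the sleeping shares match, the ratio itself need not move, but most of the data behind it are lost. The article gives no data from which to say which case applies.

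**The case against.** The strongest reply is that this is a loosely worded sentence in a condensed article. The second formula lacks the label outdoor, and a word may have been dropped. That is possible, but neither reading of the printed words gives awake people outdoors any weight, and the listed head counts fit the literal reading.

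A second reply is that little hangs on the formula. This stands, and it rules out several stronger conclusions that a reader might draw:

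- **That the trial could not show an outdoor benefit.** Raw indoor and outdoor HBR is the listed secondary outcome (Outcomes {12}). It has its own treatment model (Effects of SR on entomological endpoints), and the adjusted analysis is run in addition.
- **That diversion would be missed.** Diversion is assessed in the buffer-zone cohorts and by buffer-zone light traps. No diversion analysis uses adjusted HBR.
- **That all evening exposure is discarded.** The indoor formula still counts everyone indoors who is not under a net, from 6 pm on.
- **That the lost exposure is the product's one target.** Emanators hang on interior walls, and the Discussion names early-evening and/or outdoor biting, so the lost part is only one strand of the rationale.
- **That the separate indoor and outdoor denominators are themselves an error.** The general definition can mean a proportion worked out within each household, and a location-specific share is a coherent measure. Dividing by all household members is one reading and is not clearly the plan's own.
- **That hours with nobody outdoors, where the ratio is 0/0, expose a gap.** Handling such hours is routine detail for an analysis plan.

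It is also fair to say that all the counts in the illustrations are assumed, and that they show lost exposure and not a measured bias in the SR/placebo ratio.

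**Conclusion.** The point holds for the outdoor numerator only. As written, the formula contradicts both the definition that it is meant to apply and the indoor formula beside it. The loss of awake outdoor exposure is complete in any hour when nobody outdoors is asleep; this follows from the formula and needs no assumption. The share of the night's outdoor exposure that is lost depends on how many people sleep outdoors, which the article does not report. In the assumed profile, 0 to 1.0 of 14 is kept when 0% to 25% of the later outdoor people sleep.

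The adjusted outdoor SR/placebo ratio would therefore describe outdoor sleepers and not people outdoors. Its direction and size of error cannot be stated from the article. The matter is modest in weight, because the analysis is supplementary, but it is a stated rule that would be followed as printed and it should be corrected.

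**What to change.** Count everyone outdoors, awake or asleep, as at risk in the outdoor numerator, leaving out only people under a net outdoors if that is recorded. The article lists a net count for indoors only.

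With a purely outdoor denominator this makes the weight about 1, so adjusted outdoor HBR nearly equals raw outdoor HBR. If a true household behaviour adjustment is wanted, a workable form for each hour is:

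- Indoor: indoor raw HBR × (indoors, not under a net) / (indoors + outdoors)
- Outdoor: outdoor raw HBR × (outdoors, unprotected) / (indoors + outdoors)

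In the assumed evening hour this gives 2 × 2/6 = 0.67 indoors and 3 × 4/6 = 2.0 outdoors. Hours with nobody outdoors but someone indoors then contribute zero to the outdoor value. The text should also label the second formula as outdoor and state which denominator is meant.

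The cost is a change of formula wording and slightly more analysis work. The hourly head counts indoors, outdoors and under a net indoors are already collected, so no data collection changes.
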